
## Participant timeline

Abbreviations: *CT* computed tomography, *VA* visual acuity, *CS* contrast sensitivity, *IR* infrared, *FAF* fundus autofluorecence, *OCTA* optical coherence tomography angiography, *SD-OCT* spectral domain optical coherence tomography, *anti-VGEF* anit vascular endothelial growth factor, *MRI* magnetic resonance imaging, *cIMT* carotid Intima media thickness, *PWV* pulse wave velocity, *ABI* ankle brachial index, *ASAT* aspartate aminotransferase, *ALAT* alanine aminotransferase (Table 1).

**Table 1 Tab1:** Schedule of study procedures and visits

Time:		M0	M6	M12	M18	M24
Visit:	1 (screening)	1		2		3
Eligibility screening	X					
Informed consent	X					
Low dose CT of legs and head (siphons)		X				X
Dermatological measurements						
Skin biopsy		X				X
Ophthalmological measurements						
Measurement of VA and CS		X				X
Fundus imaging (IR, FAF and OCTA)		X				X
SD-OCT scanning		X		X		X
No. of anti-VEGF injections		X	X	X	X	X
Vascular measurements						
Cerebral MRI		X				X
cIMT, PWV, PWA, and ABI		X				X
6 min walk test		X				X
WELCH questionnaire		X				X
Laboratory measurements						
Plasma Pyrophosphate		X				X
Desmosine		X				X
Laboratory measurements for safety monitoring (Calcium, 25-OH vitamin D, Creatinine, Phosphate, Magnesium, Albumin, ASAT, ALAT)	X			X		X
EQ-5D		X				X
PROMIS 10		X				X
PROMIS PF		X				X
USER P		X				X

*CT* computed tomography, *VA *visual acuity, *CS *contrast sensitivity, *IR* infrared, *FAF *fundus autofluorecence, *OCTA* optical coherence tomography angiography, *SD-OCT* spectral domain optical coherence tomography, *anti-VGEF* anit vascular endothelial growth factor, *MRI* Magnetic resonance imaging, *cIMT* carotid Intima media thickness, *PWV* pulse wave velocity, *ABI* ankle brachial index, *ASAT* aspartate aminotransferase, *ALAT* alanine aminotransferase

## Sample size calculation

Sample size calculations for the TEMP-PREVENT trial were performed using the results of the TEMP trial [19]. The TEMP trial showed a relative difference in mean siphon and leg calcification of 14% between placebo and control for 1 year of treatment. We anticipate calcification to increase in a non-linear manner over the course of the life of a PXE patient. Therefore, for the sample size calculation, we assumed a lower relative difference of 10% over 2 years. With this difference, a power of 80% and a two-sided alpha of 0.05, we would need 33 subjects per arm. With an expected dropout rate of 15%, we would need 38 subjects per arm, resulting in 76 subjects for the trial. All statistical analyses will be performed using R, R Foundation for Statistical Computing, Vienna, Austria.

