A proof-of-concept study demonstrated that etidronate reduced soft tissue calcification in an *ABCC6* -/- mice model [17]. This finding was confirmed in a randomized, double-blind, placebo-controlled clinical trial in PXE patients [18]. After 1 year of treatment, arterial calcification had decreased by 4% (IQR, − 11% to 7%) in the etidronate group and increased 8% (IQR, − 1% to 20%) in the placebo group [18, 19]. Arterial calcification was, however, not a primary endpoint. Moreover, the trial included only PXE patients with extensive arterial calcification, resulting in a relatively older and more affected population. It is unclear if arterial calcification is equally inhibited in a young adult population with fewer PXE manifestations. Moreover, etidronate only inhibits the growth of calcification and does not reverse it, so prevention of further ectopic calcification early on may be even more beneficial than inhibiting it at a late stage. Another benefit of a young trial population is that calcification of Bruch’s membrane is better visible in eyes that show no gross structural damage to the macula, such as choroidal neovascularization or pigment epithelium or retinal atrophy, as often happens in later stages of PXE.

Therefore, in the TEMP-PREVENT trial, we aim to determine the effect of etidronate treatment in PXE patients with minimal or no existing arterial calcification on the development and progression of arterial calcification, and also on ocular calcification in Bruch’s membrane, dermatological calcifications, and cardiovascular outcomes.

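### The 15% dropout allowance is computed as 33 × 1.15 = 38 per arm; keeping 33 needs 33/0.85 = 39, and the 33 itself matches a one-year spread used for a 24-month change

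*Protocol article*

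**What the plan says.** The protocol article, under Sample size calculation, takes its planning values from the earlier one-year trial of etidronate in PXE: "Sample size calculations for the TEMP-PREVENT trial were performed using the results of the TEMP trial". That trial is said to have shown a "relative difference in mean siphon and leg calcification of 14% between placebo and control for 1 year of treatment". For the present trial the effect is lowered: "we assumed a lower relative difference of 10% over 2 years". The result is then given: "With this difference, a power of 80% and a two-sided alpha of 0.05, we would need 33 subjects per arm". The dropout step follows: "With an expected dropout rate of 15%, we would need 38 subjects per arm, resulting in 76 subjects for the trial".

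The section names no SD. The only spread for this outcome anywhere in the article is under Background and rationale, where the earlier trial's one-year changes are a median fall of 4% with etidronate (IQR −11% to 7%) and a rise of 8% with placebo (IQR −1% to 20%).

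Four other places bear on the point. Study population says that anyone withdrawn will be replaced. Data collection says that stopping study medication does not count as withdrawal and that follow-up continues. Statistical analysis plans a t-test or Mann–Whitney U test on the change from baseline to 24 months. Trial status says that the last patient was recruited on 4 December 2024 and that the last visit is due in December 2026.

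**The concern.** Two things stand out. First, 38 is what one gets by adding 15% to 33. Adding 15% and then losing 15% of the larger number does not return to 33, so the stated allowance falls short of its purpose.

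Second, the effect was explicitly changed for a longer trial in a different population, but nothing is said about the spread. Here the interval is 24 months instead of 12. The article describes the earlier patients as older and more affected, whereas this trial targets patients with little or no arterial calcification. A percentage change can be more variable over a longer interval and from small baselines. If the planning SD is a one-year value, the stated 80% could be optimistic by more than the dropout slip alone. At stake is how much weight a non-significant result can bear.

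**Working it through.** **Inputs from Sample size calculation.** Difference 10 percentage points, power 80%, two-sided alpha 0.05, 33 per arm, dropout 15%, 38 per arm, 76 in total. Allocation is 1:1 (Allocation section).

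**Inputs from Background and rationale.** One-year IQR widths: 7 − (−11) = 18 for etidronate and 20 − (−1) = 21 for placebo.

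**Step 1: dropout.**
- The stated figure: 33 × 1.15 = 37.95, so 38.
- Enrolment that leaves 33 after 15% loss: 33/(1 − 0.15) = 38.82, so 39 per arm and 78 in total.
- What 38 leaves: 38 × 0.85 = 32.3 per arm.
- Loss that 38 can absorb: 1 − 33/38 = 13.2%.

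**Step 2: which SD gives 33?** Assuming normality, SD = IQR width/1.349.
- Etidronate: 18/1.349 = 13.34. Placebo: 21/1.349 = 15.57.
- Pooled: √[(13.34² + 15.57²)/2] = 14.50.
- Normal approximation: n = 2 × [(1.960 + 0.842) × 14.50/10]² ≈ 33.0, so 33 per arm. The stated figure is reproduced.

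Working backwards, 33 per arm at 80% power implies an SD of 14.50 by the normal approximation, or 14.28 if a t-test calculation was used. At SD 14.50 an exact t-test calculation needs 33.98, so 34.

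**Step 3: power with 32.3 per arm, difference 10.**

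| Planning SD | Method | Power |
|---|---|---|
| 14.50 | normal approximation | 79.2% |
| 14.50 | t-test | 77.9% |
| 14.28 | t-test | 79.1% |

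**Step 4: if the 24-month SD is larger.** The multipliers are assumptions; the article gives no 24-month SD. Power is by t-test with 32.3 per arm.

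| Multiplier of 14.5 | SD | Power |
|---|---|---|
| 1.0 | 14.5 | 78% |
| 1.1 | 15.9 | 70% |
| 1.2 | 17.4 | 62% |
| 1.41 | 20.5 | 49% |

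The multiplier 1.41 = √2 corresponds to independent changes of equal variance in the two years, with the whole one-year variance treated as real change. Scan-to-scan error would not accumulate in this way. If half of the one-year variance were such error (also an assumption), the SD would be 14.5 × √1.5 = 17.8 and power about 61%.

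**The case against.** The dropout slip is one patient per arm. Withdrawn patients are to be replaced, patients who stop medication stay in follow-up, and multiple imputation is allowed, so the number analysed might not fall to 32. This is fair as to size, but it does not correct the stated figure: the section allows for dropout on top of the replacement rule and does so with the wrong operation. With recruitment closed in December 2024 and the last visit due in December 2026, a replacement enrolled now could not complete 24 months on that schedule. Replacements before closure were possible, but the article reports none.

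The stronger objection concerns the SD. A reader might infer that the one-year spread is the only route to 33 and that this proves a carry-over. The article does not support that.
- Any SD of roughly 14.3 to 14.5 (normal approximation), or slightly lower by t-test, gives 33.
- The IQR limits are rounded. Widths one point narrower or wider in both arms (17 and 20, or 19 and 22) give 30 to 37 per arm.
- The conversion assumes normality, and the etidronate IQR is not symmetric about its median.
- The 14% in the sample size section is not the 12-point gap (8 + 4) in the Background, so the planners used a figure that the Background does not show and may have had its SD too. An article may also leave the SD to the full protocol.

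These points stand. The match is an inference, and the missing SD is not in itself counted as an error here. It is also fair that 77.9% mixes two methods if 33 came from the normal formula, which is why a range is given above.

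**Conclusion.** The dropout arithmetic is wrong on the article's own figures: 39 per arm (78 in total) should stand where 38 (76) does. With 38 randomised and 15% lost without replacement, power is about 78 to 79% instead of 80%, a shortfall of 1 to 2 points on a planning SD of 14.28 to 14.50. That is minor in size.

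The SD point is conditional. The implied SD agrees with the earlier trial's one-year value, while the effect was reset for 24 months and a different population. This suggests that the spread was not reset, but does not prove it. A reader might go further and conclude that the trial lacks 80% power by a wide margin. The documents do not support that as a fact: 70%, 62% and 49% hold only if the 24-month SD is 10%, 20% or 41% above 14.5, and the article gives no such SD. They show how sensitive the power claim is to an input that is not stated; they do not forecast the trial's power.

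**What to change.** Recruitment is closed, so correct the statement and leave the design as it is. In the sample size paragraph, or in the analysis plan and results paper:
- say that 15% dropout on 33 per arm calls for 39 per arm (78 in total), and that the 38 per arm planned leave about 32 completers at that rate, with about 78 to 79% power on the planning SD;
- name that SD and its source, and say whether it describes a one-year or a 24-month change;
- give power over a range of 24-month SDs, for example 14.5 to 20.5, marked as hypothetical.

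The cost is one paragraph and a slightly less favourable power figure. No extra patients are needed and trial conduct does not change.

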## Assignment of interventions

### Allocation

Randomisation will be performed 1:1 using computer-generated block randomization with variable block sizes by the Clinical Drug Research Unit of the UMCU. Participants and researchers are both blinded to treatment allocation. Participants are enrolled by the research physician. The research physician is not involved in the randomisation procedure.

### Blinding

Patients and the study team will be blinded to treatment allocation. The study visits will be conducted by the research physician who is blinded to treatment allocation. The deblinding list will be kept in the Department of Clinical Pharmacy. Deblinding of study medication of individual participants is only possible in the case of a medical emergency, in which deblinding has consequences for the medical treatment of the participant.

## Data collection

An overview of visits is shown in Table 1. At baseline, patients visit the UMCU, and after taking the screening for eligibility and signing of informed consent, study data is collected. Patients undergo a CT scan, skin biopsy, ophthalmologic measurements plus retinal imaging, carotid ultrasound, pulse wave analysis, ankle brachial index measurement, 6-min walking test, a 7T-MRI of the brain, cognitive testing, and laboratory evaluation, all on the same day. After the first visit, questionnaires are sent out via e-mail. At 6 and 18 months, the patients are called to evaluate the number of anti-VEGF injections used or if any adverse events have occurred. At 12 months, patients visit the UMCU again for laboratory testing and retinal OCT scanning. At 24 months, all testing performed at baseline is repeated. Participants may withdraw from the study for any reason at any time. Early discontinuation of the study medication is not a reason for withdrawal from the study, and follow-up visits will be continued as scheduled. 

For data collection, e-CRFs are used in Electronic Data Capture of Castor (Amsterdam, the Netherlands). Digital pseudonymized files are stored within the UMCU Research Folder Structure. Independent external party Julius Clinical will conduct data monitoring. All data will be handled confidentially. Study information will not be released outside of the study without the written permission of the participant, except as necessary for monitoring. Subject data will be stored using the subject identification codes. The key to the codes will be kept by the researcher and the data manager. The subject identification code list will be treated confidentially at all times, and by the GDPR.

## Statistical analysis

Descriptive data will be presented as numbers and percentages for categorical data, mean and standard deviations for normally distributed continuous data, or median and interquartile ranges for non-normally distributed continuous data. Data will be analyzed applying the intention-to-treat principle. When missing data occurs, potential patterns will be analyzed and appropriate methods used accordingly (i.e., complete case analyses or multiple imputation) [44]. Researchers will be blinded during statistical analysis. The mean change (delta) from baseline to 24 months will be calculated for both groups for all primary and secondary endpoints. These deltas will be analyzed with a two-tailed Student’s *t*-test or Mann–Whitney *U* test as appropriate. In the case of relevant baseline differences, adjustments will be made with regression models. Both adjusted and unadjusted models will be presented. Also, if the numbers are sufficient, subgroup analyses will be performed in patients with different PXE phenotypes (predominantly ophthalmological phenotype, predominantly dermatological phenotype, predominantly vascular phenotype).

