## Discussion

The TEMP-PREVENT trial will provide insight into the effect of 24 months of treatment with etidronate in young adult patients with PXE.

Previously, the TEMP-trial has shown that a year of etidronate treatment in PXE patients gave a reduction in arterial calcification of 4% (interquartile range [IQR], − 11% to 7%) when compared to placebo. This trial did, however, exclusively enroll patients with measurable arterial calcification, comprising, therefore a relatively older and more profoundly affected study population. It remains uncertain to what extent arterial calcification can be halted in a young adult population. 

A young adult study population has the additional advantage that the retina is not yet, or at least to a lesser degree, affected by choroidal neovascularization and atrophy [45]. The TEMP trial showed a difference in neovascularizations between the etidronate (1) and placebo group (9); however, post hoc analysis showed this was likely not an effect of etidronate but could be explained by the unequal distribution of patients more at risk of CNV activity among the two groups [46]. Using newly developed techniques in measuring reflectivity of Bruch’s membrane in patients without extensive structural damage of the macula, the aim is to better study the effect of etidronate on ophthalmologic manifestations in PXE patients.

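### Adjustment is triggered by observed baseline imbalance, and no single analysis is named to carry the primary conclusion

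*Protocol article*

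**What the plan says.** The Statistical analysis section of the protocol article takes the change from baseline to 24 months for every primary and secondary endpoint. It compares the arms with a two-tailed t-test or a Mann–Whitney test and gives no rule for choosing between them. On covariates it says: "In the case of relevant baseline differences, adjustments will be made with regression models". It does not define when a difference is relevant, and it names no covariate. It continues: "Both adjusted and unadjusted models will be presented". Neither result is designated as primary there or elsewhere in the article. The same section says that researchers are blinded during the analysis.

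Three other places bear on the point:

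- Outcome measures defines the primary endpoint as a percentage change in calcification volume.
- Sample size calculation expects calcification to rise non-linearly over a patient's life.
- Allocation describes blocked 1:1 randomisation and names no stratification factor.

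**The concern.** In a randomised trial, an observed baseline difference is a chance event. What makes a covariate worth including is that it predicts the outcome. A trigger based on imbalance therefore adjusts for unimportant variables that happen to differ and leaves out important ones that happen to balance. Analysing change does not remove the issue, because change can itself depend on baseline burden or age. The article gives reason to expect this: its argument about non-linear progression makes age and disease stage plausible predictors before any data are seen.

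The second problem is that t-test, Mann–Whitney and adjusted model can give different p-values, and nothing says which one decides the trial. At stake are some precision in a 76-patient study and a clear answer if the results disagree.

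**Working it through.** **Inputs**

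- Difference: "we assumed a lower relative difference of 10% over 2 years", read as 10 percentage points.
- Size: "With this difference, a power of 80% and a two-sided alpha of 0.05, we would need 33 subjects per arm".
- SD of percentage change: not stated. Assumed from the earlier trial's one-year IQRs in Background and rationale (−11 to 7 on etidronate, −1 to 20 on placebo), taking normality: 18/1.349 = 13.34 and 21/1.349 = 15.57. Pooled: √[(13.34² + 15.57²)/2] = 14.50.
- Correlation r between baseline and the analysed outcome: not given. Assumed range 0 to 0.5.

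**Step 1: the plan's own figure.** n per arm = 2(1.960 + 0.842)² × SD²/Δ² = 2 × 7.849 × 210.2/100 = 33.0, so 33. The exact t-test version needs 34. The stated 33 is thus consistent with an unadjusted two-group comparison at SD 14.5, with no credit for adjustment. Adding 15% (33 × 1.15 = 37.95) gives the stated 38.

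**Step 2: power if adjustment is always made.** Adjustment multiplies the SD by √(1 − r²). Power = Φ(Δ / [SD√(1 − r²)√(2/n)] − 1.96). With n = 33 and r = 0, the ratio is 10/(14.50 × 0.2462) = 2.80.

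| r | ratio | power | n per arm for 80% |
|---|---|---|---|
| 0 | 2.80 | 80.0% | 33 |
| 0.3 | 2.80/0.954 = 2.94 | 83.6% | 31 |
| 0.5 | 2.80/0.866 = 3.24 | 89.9% | 25 |

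**Step 3: how often a trigger fires by chance.** Suppose relevant means more than 0.25 SD (assumption). The difference in baseline means has standard error √(2/33) = 0.246 SD, so the chance is P(|Z| > 0.25/0.246) = about 31%.

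**Step 4: type I error by simulation.** 33 per arm; 8000 null runs per setting; r = 0, 0.3, 0.5; normal, t with 3 df, and lognormal errors. Two assumed rules: Shapiro–Wilk p < 0.05 in either arm selects Mann–Whitney, and the 0.25 SD trigger selects the adjusted model.

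| Procedure | Rejection rate under the null |
|---|---|
| t-test, Mann–Whitney or ANCOVA, each alone | 4.2–5.4% |
| Normality pretest, applied mechanically | 4.6–5.4% |
| Imbalance trigger, applied mechanically | 3.1–5.0% |
| Trigger applied; better of adjusted and unadjusted taken when it fires | 5.2–6.2% |
| Better of t-test and Mann–Whitney | 5.6–6.8% |
| Best of t-test, Mann–Whitney and ANCOVA | 6.2–8.5% |

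**Step 5: power by simulation, 3000 runs, same difference.**

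| Errors, r | t-test | Trigger rule | ANCOVA, always | Mann–Whitney |
|---|---|---|---|---|
| normal, 0 | 78.5% | 78.0% | 77.5% | 75.9% |
| normal, 0.3 | 79.6% | 80.3% | 81.8% | 77.5% |
| normal, 0.5 | 80.0% | 83.8% | 88.8% | 78.1% |
| lognormal, 0 | 79.1% | 91.5% | 78.1% | 97.4% |
| lognormal, 0.5 | 79.2% | 91.0% | 87.6% | 90.1% |

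With normal errors, ANCOVA runs one to two points below Step 2, which uses a normal approximation. With skewed errors, ANCOVA on the raw scale can fall well below the rank test, so adjustment pays only on a suitable scale.

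**The case against.** **Covariates and test choice belong in an SAP.** Largely fair for the covariate list and the test-selection rule. But the article is not silent: it states the imbalance trigger, and an SAP would have to inherit or contradict it.

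**The type I error is not really at risk.** A reader might infer that the plan runs at 8.5%. It does not follow. That figure is the top of a range that assumes the best of three p-values is picked. Mechanical use of the rules keeps the error at or below about 5%, apart from simulation noise. Presenting both models is open reporting, and blinded analysis makes selection by direction harder. It does not remove selection, because p-values are visible with coded groups.

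**The precision loss may be small.** This stands. A reader might apply the variance ratio 2/(1 + ρ), with ρ the correlation between baseline and 24-month values, and conclude at ρ = 0.5 that 76 patients act like 76 × 1.5/2 = 57. That formula is for absolute change with equal variances, whereas the primary endpoint is percentage change. On a log scale, SD(change) = SD(baseline) × √[2(1 − ρ)], so ρ = 0.5 with an SD of change near 14.5% would mean that patients' volumes differ by only about 14.5%. Volumes plausibly vary far more, which puts ρ nearer 1. At ρ = 0.9 the ANCOVA-to-change variance ratio (1 + ρ)/2 is already 0.95.

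**Two further inferences fail.**

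- The Discussion's remark that a neovascularisation difference in the TEMP trial "could be explained by the unequal distribution of patients more at risk of CNV activity among the two groups" concerns one ocular result. It does not show that imbalance misled that trial's calcification result.
- The 12-month laboratory values are not unused. Table 1 labels them safety monitoring, and Data monitoring includes laboratory parameters in the interim safety reviews.

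**Conclusion.** The concern holds as a defect in a stated rule. Adjustment depends on an undefined observed imbalance, the test depends on the data, and no result is named as decisive. Nothing else in the article resolves this.

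Its size is uncertain. Under a 10-point difference, SD 14.5 and 33 per arm, consistent adjustment adds nothing at r = 0, about 4 power points at 0.3 and about 10 at 0.5. The SD is borrowed from one-year data in an older, more affected population, and r is unknown. Type I error would be about 6 to 8.5% only if the headline could be chosen freely among the three analyses. The article does not say that it will be chosen that way; it fails to rule it out.

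**What to change.** Delete the imbalance trigger. Before unblinding, name one primary model that adjusts for the endpoint's baseline value and age whatever balance is observed.

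For the primary endpoint, fix the scale in advance so that it keeps relative change and handles skew and zero baseline volumes. Zeros are likely, because the stated aim includes patients with minimal or no arterial calcification and percentage change is undefined at zero. One workable form regresses log(24-month volume + c) on treatment, log(baseline volume + c) and age, with c fixed beforehand. The treatment coefficient is the same as when the log ratio of the two volumes is the outcome with the same covariates, so the relative-change question is preserved. ANCOVA of raw 24-month volume would not do this and could be dominated by a few patients.

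Make the unadjusted t-test and the Mann–Whitney test sensitivity analyses, and say that they do not decide the primary conclusion.

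The cost is wording in the protocol or SAP, a few degrees of freedom and a justified choice of c. The covariates are already collected. The article schedules the last visit for December 2026; after unblinding the choice can no longer be made credibly.
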